### **Organisation of care**

In England, there has been a financially incentivised change in the organisation of more structured primary care for some physical disorders such as diabetes and cardiovascular disease identified in the Quality Outcomes Framework [44]. There is debate about how much these financial incentives have changed the process and outcomes of such care [45,46]. In contrast the same organisation of care does not routinely happen in the management of mental disorders although there are additional psychological treatment resources to help primary care manage depression and anxiety [47]. Furthermore, the interventions that have demonstrated clinical and economic benefits in persistent frequent attenders with depression or functional somatic symptoms required considerable reorganisation of care and workforce training and development. Yet most practice staff, other than GPs, have no formal training in the assessment and management of mental disorders, and few GPs have training in the management of functional somatic symptoms or persistent frequent attendance [48]. There is a need for specialist mental health support for practice staff managing these patients [49] but the current tariff system does not reward mental health staff to do such work unless there is face to face contact with the patient [50].

Despite the evidence for high consumption of secondary health care resources among persistent frequent attenders in primary care, there has been no formal economic study of persistent frequent attendance. Without such a study, the potential costs and benefits of mental health intervention to support primary care doctors to manage these patients cannot be properly planned and subsequently evaluated. Furthermore there is a need to understand how different practices organise the care for these patients and how patients make their decisions on who to consult in order to tailor interventions for persistent frequent attenders could be applied to a wide range of practices in England.

### **Terminology**

The research literature uses the term “frequent attender” which has a variety of definitions from study to study. We have used this term in the above review. However, a panel of service users reviewing our study documents found the term “frequent attender” to be offensive as it implies a criticism of the patient for attending too often. The term may be seen as pejorative and blaming the patient [19-21,51]. Instead the service user panel recommended a more neutral term “regular attender” which we now use below.

### **Study objectives and hypothesis**

#### **Objectives**

The primary objective is to gain a better understanding of the needs and implications for the health service of regular attenders in primary care in terms of the costs of health care, patterns and chronicity of health care consultation, clinical characteristics, reasons for consultation, and organisation of their care by the GP and practice.

Secondary objective are to:

1. Estimate the cost to the health service of regular attendance in primary care and to examine the pattern and chronicity of regular attendance.

2. Clinically characterise people with regular attendance in primary care compared to normal attendance.

3. Explore motivations, reasons for regular attendance in primary care and patient experiences of consultation.

4. Explore practice characteristics, organisation of care and other barriers and drivers on the management of regular attenders and other complex patients with multiple morbidity.

5. Use CBT formulation to understand the development of regular attendance and its relationship to other health and social problems;

6. Develop a descriptive typology of the development and reasons for regular attendance using information derived from the qualitative interviews and CBT formulation;

7. Explore the acceptability, feasibility and clinical utility of CBT formulation and a treatment plan delivered jointly by the practice and the cognitive behaviour therapist for regularly attending patients.

#### **Hypotheses**

1. Most patients with regular attendance in primary care show chronic patterns of health care use with a duration of three or more years.

2. Compared to age, gender and practice matched normal attender controls, regular attenders are more likely to have depressive and anxiety disorders, somatoform disorders, high health anxiety, two or more active physical health problems, and a history of trauma or abuse in childhood or adulthood.

3. Compared to normal attender controls, regular attenders will incur up to five times the health care costs over the preceding 10 years but have a lower quality of life on the EQ5D.

4. Cognitive behaviour formulation and joint treatment between a cognitive behaviour therapist and a GP are feasible, acceptable and have clinical utility for regular attendance.

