### **Case control study of regular attenders and normal attenders**

#### **Inclusion criteria**

1. Regular attenders

· 30 or more face to face contacts with GP within the last 2 years established from the practice electronic record.

· Aged 18 years old and over.

· Consents to take part in the study

2. Normal attenders

· Between six and 22 face to face contacts with GPs over two years, established from the practice electronic record. A previous study of 828 consecutive attenders from eight Nottinghamshire practices revealed a median attendance of eight face to face consultations with GPs with approximately two thirds of the sample consulting between three and eleven consultations. Therefore we selected a normal consulting control group from patients who attended face to face appointments with the GP between six and 22 occasions.

· Aged over 18 years or older

· Consents to take part in the study

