In addition, information on active physical health problems currently and in the last two years, body mass index, smoking and alcohol consumption, and exercise will be extracted from practice records. The health care records will be examined 12 months later to ascertain health care use in the 12 month period following baseline assessment. Secondary health care use will be ascertained by exploring health care records over the preceding 10 years and prospectively over the next 12 months in all local secondary care services and nationally from Hospital Episode Statistics collected by the Department of Health for England.

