We will examine health and social care costs over the preceding 10 years from primary care records in both the regular attenders and normal attenders who have consented to the study. For each preceding year over the last 10 years, information will be collected on the number of contacts and missed appointments with the GP (at surgery, home or telephone contacts), practice nurse, community nurses, counsellors, physiotherapists, occupational therapists, social workers, community workers, NHS Direct, drop-in centres and home help, prescriptions, investigations, secondary care in-patient and out-patient care, and emergency care. Practice based primary care information is likely to be more accurately recorded than contacts that happened outside the practice. However we intend to trawl for the GP referral letters to obtain estimates of secondary care usage and we will also collect contact information for each participant from all local hospitals. Full and complete anonymised data sets of ten year medical records will be processed using a replicable method of electronic data collection that has been developed specifically to answer a number of health and economic and clinically important questions. In addition this data will provide us with a detailed insight into patients resource use in primary as well as secondary care. We will be able to check the data retrieved electronically with the data collected from the modified Client Services Receipt Inventory (CSRI) [55] and therefore check the degree to which care outside the practice may be underestimated. Similarly the analysis of reporting of contacts with primary care at interview compared to the primary care record will explore whether or not regular attenders are underreporting health contacts compared to normal attenders as reported previously [21,51]. To examine agreement in some key information of service use between patient recalls and primary care records, we shall use non parametric correlation analysis which includes Spearman’s rank correlation coefficient, Kendall tau, and Kappa coefficient for different outcome measures where it is appreciated. We will explore the effect any under-reporting by regular attenders may have had on health and social care costs.

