### **Intervention**

The intervention will be offered at one of two levels to all regular attender patients who complete the baseline assessment and case record examination outlined in case study one (Figure 1). It will not be offered to normal attenders. Level 1 intervention will be offered to all regular attenders provided they consent to further assessment and therapeutic intervention by one of three cognitive behaviour therapists, currently have functional somatic symptoms, depressive or anxiety disorders, do not have an urgent need for other health care and are not already receiving mental health care as shown in Figure 1.

In level 1 interventions the cognitive behaviour therapist will formulate the reasons for regular attendance in both primary care and secondary care settings in consultation with the GP who usually sees the patient (Figure 2). In keeping with recent developments in CBT formulation, the latest problem-specific models will be used to formulate or a generic model applied for cross-diagnostic issues [59]. Whichever CBT model is used emergent formulations and intervention plans will focus on addressing three areas: 1. The primary focus of the formulation is on the pattern of regular consultation behaviour of the patient with health services rather than somatic distress or health anxiety; 2. The formulation takes a developmental perspective seeking to understand how the regular consultation behaviour arose and is maintained [60]; 3. Consulting behaviour of the patient is understood primarily in terms of its social function from the patient’s perspective the responses of primary care, secondary care and social environment to the consulting behaviour.

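### The two years used to select the groups sit inside the 10-year cost window and the three-year duration, so part of any excess is built in, and hypothesis 3 sets a ceiling on the cost ratio but no floor

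*Protocol article*

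**What the plan says.** All references are to the protocol article.

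- **Hypotheses.** Hypothesis 3 says that, compared with normal attenders, "regular attenders will incur up to five times the health care costs over the preceding 10 years", and adds that their EQ5D quality of life will be lower. Hypothesis 1 says that most regular attenders "show chronic patterns of health care use with a duration of three or more years".
- **Inclusion criteria.** Cases need "30 or more face to face contacts with GP within the last 2 years established from the practice electronic record". Controls need "Between six and 22 face to face contacts with GPs over two years, established from the practice electronic record". The control band is justified by an earlier survey that "revealed a median attendance of eight face to face consultations with GPs".
- **Health economics in case–control study.** "We will examine health and social care costs over the preceding 10 years from primary care records". GP contacts are among the items counted, and use is collected separately for each of the ten years. No sentence starts the window before the selection years or sets them apart.
- **Procedures and measures.** "The health care records will be examined 12 months later to ascertain health care use in the 12 month period following baseline assessment".
- **Intervention.** "The intervention will be offered at one of two levels to all regular attender patients who complete the baseline assessment". Normal attenders are not offered it.

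**The concern.** A comparison of past use between groups defined by past use is partly circular when the defining period is inside the period compared. Here the last two of the ten costed years are the years that made a patient a case or a control. Some excess in GP contacts, and so in cost, would appear even if the two groups had been alike in every earlier year. Likewise, if the qualifying years count towards the duration in hypothesis 1, the entry rule has already met two of the three.

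The wording of hypothesis 3 adds to this. It gives an upper figure for the cost ratio and no lower one, so a small or absent excess would not clearly count against it.

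This matters because the economic result is meant to be used. The health economics section treats the cost of this group as the basis for willingness to pay for an intervention, and the Discussion says it will set the economic parameters for developing one. A single 10-year ratio does not show whether the excess is long-standing or mainly recent.

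**Working it through.** **The plan's own figures.** The article gives no cost figures and no power or precision statement for hypotheses 1 or 3. Its one power statement (48% vs 25%, 100 per group, 90%) concerns mental disorder. It reproduces (99 per group with continuity correction; 90.4% power by Fisher's exact test at 100 per group) and is not at issue here.

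**Inputs**
- Case contacts over two years, A: at least 30 (Inclusion criteria).
- Control contacts over two years, c: 6 to 22 (Inclusion criteria). The band midpoint is 14. The survey median of 8 gives 16 if it is annual. The article does not state the period; annual is assumed because doubling the survey's 3 to 11 gives the 6 to 22 band.
- Window: 10 years, of which 2 are selection years (20%).
- Null scenario (assumed): in the other eight years both groups consult at the control's yearly rate, c/2.

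**Step 1: contacts in the index window.** Ratio = A/c. The smallest possible value is 30/22 = 1.36. At c = 16 it is 30/16 = 1.88, and at c = 6 it is 30/6 = 5.0.

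**Step 2: contacts over 10 years with no earlier difference.** Ratio = (A + 8·c/2)/(c + 8·c/2).

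| Case A | Control c | Calculation | 10-year ratio |
|---|---|---|---|
| 30 | 22 | (30 + 88)/(22 + 88) | 1.07 |
| 30 | 16 | (30 + 64)/(16 + 64) | 1.18 |
| 30 | 14 | (30 + 56)/(14 + 56) | 1.23 |
| 30 | 6 | (30 + 24)/(6 + 24) | 1.80 |
| 40 | 22 | (40 + 88)/(22 + 88) | 1.16 |
| 40 | 6 | (40 + 24)/(6 + 24) | 2.13 |

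With the index years removed, the ratio is 1.00 in every row.

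**Step 3: total cost.** Let s be the GP share of control cost (not given; 20% and 50% assumed), with costs flat over time and all other costs equal between groups. The built-in 10-year cost ratio is 1 + 0.2·s·(A/c − 1).
- s = 0.2: 1 + 0.04 × 0.36 = 1.01 (1.015 before rounding) to 1 + 0.04 × 4 = 1.16.
- s = 0.5: 1 + 0.1 × 0.36 = 1.04 to 1 + 0.1 × 4 = 1.40.

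**Step 4: could selection alone give fivefold?** Even with s = 1, a ratio of 5 needs A/c = 1 + 4/0.2 = 21. Against c = 16 that is 336 contacts in two years, and against c = 6 it is 126. As a group average this is far outside anything the entry rule implies.

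**Step 5: hypothesis 1.** Required duration 3 years, minus 2 years met at entry, leaves 1 year that the data must decide.

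**Step 6: wording of hypothesis 3.** Ratio above 5: contradicts it. Ratio between 1 and 5: agrees. Ratio of 1 or below: agrees literally, although the contrast with lower quality of life suggests that an excess was meant.

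**The case against.** **The burden question needs the index years.** The first secondary objective is to estimate the cost of regular attendance, and the health economics section presents a burden-of-illness study. The index years are the only ones in which every case is known to be a regular attender. Dropping them would answer a different question. This stands, so the 10-year total should be kept and the split reported beside it.

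**A yearly breakdown is already possible, and the full plan may specify it.** This is partly right. Use is collected for each year, and no sentence commits to one pooled test. But the hypotheses as printed name the 10-year span and a ceiling, and an unseen plan could make them informative only by rewording them.

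**Stronger readings that the documents do not support.**
- A reader might infer that hypothesis 3 can never be refuted. A ratio above 5 would refute it, and its EQ5D half is fully testable.
- A reader might infer that hypotheses 1 and 3 are true by construction. Eight of the ten years and all non-GP costs are not fixed by selection, and hypothesis 1 still needs a third year, in most patients, that entry does not supply.
- A reader might add the 12 months after baseline to the same charge. Hypothesis 3 covers only preceding years. An intervention meant to reduce consultation would lower later use in cases, which works against hypothesis 1. The aim of reducing the need to consult is also stated in the description of level 1; level 2 is a preliminary formulation and suggested plan for the GP.
- A reader might expect case use to fall back anyway. The article reports such improvement for patients defined over 12 months, but its Background says that attendance lasting two years usually persists for another.

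**Conclusion.** The point holds in a limited form. The selection years lie inside the outcome window, so part of any excess is built in: at least 1.36 on GP contacts in the index window, and about 1.07 to 1.80 over ten years for a case at the entry threshold if the groups did not differ earlier. On total cost it is about 1.01 to 1.40 under assumed GP shares of 20% to 50%. These figures rest on equal use in the other eight years, flat costs and equal non-GP costs; they illustrate the size and are not estimates. They would not explain a large cost ratio, but they could account for a small one. The cost half of hypothesis 3 is not clearly contradicted by any ratio of 5 or below. For hypothesis 1, one of the three years remains open, and the text does not say whether the qualifying years count.

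The post-baseline year is a separate, smaller matter. Regular attenders but not controls are offered the intervention, so that year does not show untreated persistence and would tend to understate it.

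**What to change.** 1. Keep the 10-year total as the burden estimate. Beside it, report the two index years and the eight pre-index years separately, and rest any claim of long-standing excess cost on the pre-index years.
2. Restate the cost half of hypothesis 3 as a ratio of mean costs above 1, estimated with a 95% confidence interval (a bootstrap interval would suit skewed costs), with five as a reference value to compare with the interval.
3. Define the duration in hypothesis 1 and judge it on whether the regular-attendance rate (30 in two years, or 15 a year pro rata) was met in the year or years immediately before the index window.
4. Separately, report the 12 months after baseline as post-intervention use, by level 1 and level 2, and not as natural history.

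The cost is wording and a few extra table rows, because use is already collected by year. The downside is that the reported excess may be smaller and the pre-index estimate less precise.

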#### **Method**

The study was given full ethics approval by the Nottingham 1 NRES Committee (reference number 11/EM/0392).

#### **Study design**

The study consists of four parts (Figure 1):

1. A clinical and economic case control study of regular attenders and normal attenders including examination of health care records over the previous 10 years.

2. A qualitative study of patient’s reasons for regular attendance.

3. A qualitative study of primary care practice staff to explore the organisation of care for regular attenders.

4. A feasibility, acceptability and clinical utility study of cognitive behaviour therapy formulation and treatment alongside joint patient management between the GP and therapist in regular attenders.

**Figure 1 F1:**
[figure not shown]
Design of the study.

#### **Selection of practices**

Five practices will be purposefully selected to obtain diversity in existing organisation of care and the populations served by practices so that the assessment of need and pilot intervention may be generalised to other primary care practices in England. A large random sample of practices would not provide the opportunity to carry out detailed work in each practice. Practices will be sought to include a range reflecting differing registered patient list size, patients of differing social and ethnic diversity, and affluence or deprivation; and differing practice organisational contexts, including size of practice team, salaried GPs or GP partners; full and part-time staff configurations; approaches to patient access for appointments, continuity of care, and links with mental health services.

#### **Definition of regular attendance**

Face to face attendance with the GP on 30 or more occasions in two years, excluding routine health monitoring such as international normalised ratio (INR) monitoring for patients taking warfarin, defined a group of patients who were in the top ten per cent of attenders for each of the two years [4] in two differing pilot practices. Patients with catastrophic physical illness such as cancer and serious mental illness such as schizophrenia were not represented, indicating exclusion criteria in relation to catastrophic physical illness or serious mental illness were unnecessary.

### **Case control study of regular attenders and normal attenders**

#### **Inclusion criteria**

1. Regular attenders

· 30 or more face to face contacts with GP within the last 2 years established from the practice electronic record.

· Aged 18 years old and over.

· Consents to take part in the study

2. Normal attenders

· Between six and 22 face to face contacts with GPs over two years, established from the practice electronic record. A previous study of 828 consecutive attenders from eight Nottinghamshire practices revealed a median attendance of eight face to face consultations with GPs with approximately two thirds of the sample consulting between three and eleven consultations. Therefore we selected a normal consulting control group from patients who attended face to face appointments with the GP between six and 22 occasions.

· Aged over 18 years or older

· Consents to take part in the study

#### **Exclusion criteria for both regular and normal attenders**

· Contacts for routine health care checks e.g. INR monitoring, blood pressure monitoring, changes of dressings

#### **Recruitment**

Regular attenders will be identified from each practice and matched by age, gender and practice to a normal attender to control for practice and socio-demographic characteristics, by practice staff who will write to the patients to request their participation in the study. Approximately 100 regular attenders and 100 normal attenders will be recruited. Pilot work shows that 30-40% of regular attenders will agree to be interviewed but a higher proportion of normal attenders will agree to be interviewed. The representativeness of the selected regular attenders will be compared to the overall sample of regular attenders in the practices and the overall patient lists in terms of age and gender among those aged 18 years or over.

#### **Procedures and measures**

Practice staff will identify patients who meet the inclusion/exclusion criteria from their primary care practice electronic record. All eligible regular and normal attending patients will be invited to have a baseline interview (see below). Practice staff will send eligible patients a study pack containing an invitation letter (on practice letterhead) inviting them to take part in the study, an information sheet, describing the study, a ‘consent to contact’ form and a stamp addressed envelope. If patients are interested in finding out more about the study and speaking to a researcher, they will be asked to return the ‘consent to contact form’ to the study researcher in the stamped addressed envelope provided. The consent form will also ask the patient’s permission for the researcher to access their anonymised medical records even if they do not wish to be interviewed. A researcher will then telephone the patient to discuss the study further, answer any queries they may have, and if verbal consent is given, arrange a time for interview. One reminder letter (on practice letterhead) will be posted by practice staff to eligible participants who did not respond to the initial invite. In some instances where the GP feels the patient may be suitable for the study but the patient has not responded to invitations to take part, the GP may approach the patient directly and make an appointment to see them to explain the study.

Each patient will be interviewed to explore the presence or absence of psychiatric disorder including depressive disorder, anxiety disorder and somatoform disorder [52] using a structured psychiatric interview (SCID-1) [53], the presence and degree of severity of health anxiety over the last week on the Health Anxiety Inventory (HAI) [24], quality of life on the EQ5D [54], and information on health and social care, work and benefits using the Client Receipt Service Inventory (CSRI) [55] (Table 1).

**Table 1 T1:** Baseline interview

SCID	SCID-1 for DSM-IV (Structured Clinical Interview for Diagnostic and Statistical Manual of Mental Disorders)(First et al., 1997)
CSRI	CSRI Client Services Receipt Inventory (Beecham and Knapp 2001)
EQ5D	EQ5D Standardised instrument for use as a health measurement (Euroqol group 1990)
HAI Short Week	Health Anxiety Inventory (HAI, a 14 item self-rated measure of health anxiety, Salkovskis et.al, 2002) with a score above 21 indicating severe health anxiety.

In addition, information on active physical health problems currently and in the last two years, body mass index, smoking and alcohol consumption, and exercise will be extracted from practice records. The health care records will be examined 12 months later to ascertain health care use in the 12 month period following baseline assessment. Secondary health care use will be ascertained by exploring health care records over the preceding 10 years and prospectively over the next 12 months in all local secondary care services and nationally from Hospital Episode Statistics collected by the Department of Health for England.

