### **Statistical analysis in case control study**

Burton et al. [56] showed that 93 (48%) of patients with MUS diagnosed by secondary care physicians on two or more occasions and referred at least three times in the last five years had depressive and anxiety disorder compared to 38 (25%) patients only referred once to secondary care in the previous five years (odds ratio 2.6 (95% confidence intervals 1.6, 4.1). If these groups are assumed to be similar to the regular attenders and normal attenders in the current study, a sample size of 100 regular attenders and 100 normal attenders will have 90% power to show a difference at the 5 per cent level of significance on two tailed testing.

The regular attender and normal attender groups will be compared on the proportion with mental disorder (depressive disorder, anxiety disorder, somatoform disorder, overall prevalence of mental disorder), mean number of active physical health problems, distribution of severity of health anxiety, proportion of obesity on BMI, mean scores on smoking, alcohol consumption and exercise, and utility related quality of life on the EQ5D. Univariate analysis to test differences between the two groups will be performed using *t*-test for group means or geometric means if logarithm transformation is required for variables with skewed distribution. Chi-squared test will be used for group differences in categorical variables. The accuracy of recall by patients over the previous three months will be compared to health care contacts recorded in the primary care record. There is some evidence that regular attenders may not accurately recall health care contacts and do not realise how frequently they are attending compared to practice records [21,51].

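### Active physical problems are counted from the same two-year GP record that defines the groups, so unequal recording can create or inflate the difference hypothesis 2 predicts

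*Protocol article*

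**What the plan says.** All references are to the protocol article.

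- **Group definition (Inclusion criteria).** Regular attenders have "30 or more face to face contacts with GP within the last 2 years established from the practice electronic record". Normal attenders have "Between six and 22 face to face contacts with GPs over two years, established from the practice electronic record".
- **Physical morbidity (Procedures and measures).** Practice records supply "information on active physical health problems currently and in the last two years". The same sentence says that "body mass index, smoking and alcohol consumption, and exercise will be extracted from practice records", with no period attached to these four items.
- **Hypothesis 2 (Hypotheses).** Regular attenders are expected to be more likely to have "two or more active physical health problems".
- **Comparison (Statistical analysis in case control study).** The listed comparisons include the "mean number of active physical health problems", obesity, smoking, alcohol and exercise. They use univariate t-tests or chi-squared tests.
- **Matching (Recruitment).** Age, gender and practice.
- **Interview (Procedures and measures, Table 1).** Both groups receive the SCID, HAI, EQ5D and CSRI. None is described as ascertaining physical diagnoses.

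**The concern.** The variable that separates the groups, the number of GP contacts in two years, also governs how many occasions there were for a physical problem to be entered in the record over those two years. A regular attender has at least 30 such occasions and a normal attender between 6 and 22. If some problems are recorded only when a consultation brings them up, two groups with identical true morbidity will have different recorded counts. The difference runs in the direction that hypothesis 2 predicts.

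Matching on age, gender and practice does not equalise the opportunity to be recorded. Adjusting for contact count is not available either, because the two bands do not overlap. Changing the test leaves the problem where it is.

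At stake is one component of hypothesis 2. There may also be a knock-on effect in the planned discriminant analysis, which takes forward variables found significant or important. Mental disorder and health anxiety are measured by the same interview in both groups and are not affected.

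**Working it through.** **1. The plan's own design figure.** The sample size rests on 48% against 25% with depressive and anxiety disorder, 100 per group, two-sided 5%, 90% power. The usual two-proportion formula gives 92.8% power without continuity correction and 90.5% with it (99 per group needed for 90%). The stated figure is reproduced with the correction. It concerns an interview outcome, so the present point does not alter it.

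**2. Inputs for the illustration.**
- From the protocol: regular attenders at 30 contacts (their minimum); normal attenders at 6 to 22, mid-band (6 + 22)/2 = 14; 100 per group.
- Assumed, not in the protocol: the same true number of problems in both groups, Poisson with mean 2; an independent chance q that any one contact records a given problem.

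**3. Formulas.** Chance that a problem is recorded in n contacts: r(n) = 1 − (1 − q)^n. Recorded problems are then Poisson with mean λ = 2 × r(n), and P(two or more) = 1 − e^(−λ)(1 + λ).

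Worked case, q = 0.05:
- 30 contacts: r = 1 − 0.95^30 = 0.785, λ = 1.57, P = 46.6%.
- 14 contacts: r = 1 − 0.95^14 = 0.512, λ = 1.02, P = 27.3%.
- Odds ratio = (0.466/0.534)/(0.273/0.727) = 2.3.

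**4. Range over q, 30 against 14 contacts, no true difference.**

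| q per contact | Mean recorded | Two or more | Odds ratio | Chance of a significant result, 100 per group |
|---|---|---|---|---|
| 0.02 | 0.91 v 0.49 | 23% v 9% | 3.1 | about 79% |
| 0.05 | 1.57 v 1.02 | 47% v 27% | 2.3 | about 81% |
| 0.10 | 1.92 v 1.54 | 57% v 46% | 1.6 | about 36% |
| 0.20 | 2.00 v 1.91 | 59% v 57% | 1.1 | about 5% |

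**5. Sensitivity to the controls' contact count.** At q = 0.05 the odds ratio runs from 7.9 (controls at 6 contacts) to 1.35 (at 22). At q = 0.20 it runs from 1.9 to 1.01. The protocol reports a median of eight consultations in an earlier sample. If that is per year, as the step from 3–11 to 6–22 suggests, the two-year figure is 16, and the four odds ratios become 2.5, 2.0, 1.4 and 1.06.

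**6. Sensitivity to the morbidity model.** Suppose instead that everyone has exactly three problems, so P(two or more) = 3r²(1 − r) + r³. With 30 against 14 contacts:
- q = 0.02: 43% v 15%, odds ratio 4.2.
- q = 0.05: 88% v 52%, odds ratio 6.9.
- q = 0.20: r = 0.9988 and 0.9560, giving just under 100% v 99.4%, a gap of about 0.6 percentage points.

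Near that ceiling the odds ratio ceases to be a useful scale and the difference in percentages should be read instead. Both models give a large artefact at low q and almost none at 0.20 with mid-band controls.

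**7. Lifestyle variables.** No arithmetic applies. A missing BMI or smoking entry is missing data, not a recorded absence. More contacts would tend to make these entries more complete or more recent, which does not by itself make the recorded values higher or lower.

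**The case against.** A reader might infer that regular attenders **will** show more recorded morbidity whatever the truth. The protocol does not support that. It asks for current problems as well as those of the last two years, and a current problem may have been entered long before the window. The eligibility count covers face-to-face GP contacts and leaves out routine checks, while the economics section lists nurse, telephone and other contacts. So 30 against 14 is a stand-in for recording opportunities, not a count of them. Controls have at least six GP contacts, and established conditions may be noted at almost any visit. The article does not define an active problem, so it cannot be assumed that minor or passing complaints count. All of this bears on the size, and it stands.

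A reader might also extend the point to BMI, smoking, alcohol and exercise as biased over the same two years in the hypothesised direction. The protocol gives no window for them, and hypothesis 2 names none of them. That extension fails.

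Finally, replacing the record count with self-report would be a poor exchange. Regular attenders are hypothesised to have more health anxiety and somatoform disorder, and the protocol itself doubts their recall of contacts. This stands too, and self-report should complement the record count rather than displace it.

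None of these points removes the overlap of source and window for active physical problems.

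**Conclusion.** The concern holds for active physical health problems: they are drawn from the record and two-year period whose contact count forms the groups, and no allowance is stated. Ascertainment can differ by group and can create or inflate a difference on that component of hypothesis 2.

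With mid-band controls the artefact ranges from negligible (odds ratio about 1.1 at 0.20 per contact, Poisson model) to large (about 2 to 4, or more, at 0.02 to 0.05). The upper part of that range exceeds the odds ratio of 2.6 that the protocol quotes for mental disorder. These sizes rest on equal true morbidity, independent recording at each contact and an unknown q. Only the direction is common to all the scenarios.

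For BMI, smoking, alcohol and exercise the supported point is possible differential completeness, direction undetermined. The mental-disorder, health-anxiety and EQ5D comparisons and the sample size are untouched. The change should be made, but the study does not turn on it.

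**What to change.** 1. Keep the record count of active physical problems, and pre-specify a second analysis restricted to established long-term conditions: those on a chronic-disease register or diagnosed before the two-year window.
2. At the baseline interview already planned for both groups, add one short, identical checklist of current physical conditions, height and weight, smoking, alcohol and exercise, as a complementary measure.
3. Report, by group, the completeness of each variable taken from the record.
4. State in advance that a conclusion on the physical-problem part of hypothesis 2 will be drawn only if these analyses agree.

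**Cost.** A few interview minutes and a tighter extraction rule; no new visits or staff. The checklist must be in place before interviews are held and cannot cover people who allow record access but decline interview.

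**Limits.** Self-report may itself differ by group in health-anxious patients. The pre-window restriction reduces the bias but may not remove it, because hypothesis 1 expects regular attendance to last three or more years, so earlier contacts would differ as well. This is why agreement between measures is asked for, rather than reliance on one.
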